## Abstract

**Background:**

Older adults with subjective cognitive decline (SCD) are at high risk of developing dementia and frequently experience subclinical symptoms (e.g., anxiety, depression) which are themselves associated with an increased dementia and cognitive decline risk. Our aim is to test the effects of an immersive virtual reality (IVR) and telemedicine-based multi-component intervention, that combines cognitive training and health and lifestyle education program, in individuals with SCD.

**Methods:**

To assess the efficacy of the intervention, a randomized, double-blinded controlled trial will be conducted on a sample of 75 individuals with SCD. Participants will be randomly assigned to one of three conditions: (a) multi-component intervention, including SCD-tailored cognitive IVR training plus a health and lifestyle education program, (b) cognitive-only intervention, including SCD-tailored cognitive IVR training *plus* an active control for the education program, and (c) active control intervention for both cognitive training and education program. All interventions are implemented in IVR environment and will be administered through telemedicine approach. Interventions will be provided in 20 at-home sessions (4 sessions/week, each lasting about 30 min) over a period of 5 consecutive weeks. Outcome measures will be collected before and immediately after intervention. The primary outcome is the effect of the multi-component intervention in enhancing objective cognitive functioning. Secondary outcomes include changes in subjective cognitive functioning, psychiatric symptoms, quality of life and functional neural connectivity. Users' compliance with IVR and telemedicine approach will be also evaluated, as well as individuals' factors affecting training efficacy.

**Discussion:**

Our results will provide new evidence of the efficacy of an innovative multi-component intervention integrating IVR and telemedicine in SCD individuals. Considering the relatively low costs and easy accessibility, it could be a valuable contribution to primary prevention initiatives for dementia risk reduction.

**Trial registration:**

This trial was prospectively registered at ClinicalTrials.gov on May 24, 2024 (registration number: NCT06429215).

## 1 Introduction

Dementia and cognitive decline represent a significant and growing global health crisis. The World Alzheimer Report 2024 estimated 55 million people living with dementia worldwide in 2019, with Alzheimer's disease (AD) being the most prevalent cause. This number is projected to nearly double every 20 years, reaching approximately 139 million by 2050, primarily due to population aging (“Aging and Health,” World Health Organization). Dementia and cognitive decline are leading contributors to disability and dependency among older adults, incurring an estimated cost of US$1.3 trillion in 2019 (Wimo et al., 2023); this leads to a huge burden on society and healthcare system that is destined to increase gradually over time. Despite considerable research efforts have been made to find effective disease-modifying treatments, to date there is no intervention known to cure or even reliably affect the course of dementia (Imbimbo et al., 2020). Consequently, there is increasing recognition of the need to move away from an exclusive focus on treatment of dementia toward the development of early effective prevention-interventions aimed at preventing or delaying the progression to cognitive impairment and dementia in aging population (World Health Organization, 2024). In fact, it has been estimated that up to 40% of dementia cases could potentially be prevented by addressing modifiable risk factors, including cognitive activity, diet, physical exercise, and psychiatric conditions like anxiety, apathy, and depression (Livingston et al., 2020).

Within this framework, cognitive training has garnered significant attention as a promising non-pharmacological intervention for improving cognition and potentially delaying clinical progression, whose beneficial effects are likely mediated by brain plasticity and increased cognitive reserve (Greenwood and Parasuraman, 2010). Importantly, even in older adults, synaptic structures retain modifiability, making them amenable to brain plasticity induced by cognitive training (Yin et al., 2022). Even relatively short-duration cognitive training sessions (4–8 weeks) have, in fact, demonstrated significant effects on functional connectivity in clinically healthy elderly (Kang et al., 2021; De Simone et al., 2023a; Cotelli et al., 2019; Costanzo et al., 2020; Rolandi et al., 2025). Because preventative interventions are most effective before the onset of clinically significant symptoms, subjective cognitive decline (SCD) is a crucial target for acting early interventions aimed at delaying or modifying the disease course. SCD, which is characterized by self-perceived cognitive decline without objective impairment on standard neuropsychological tests (Jessen et al., 2020), represents a high-risk factor for accelerated cognitive decline and the development of mild cognitive impairment and dementia, particularly when accompanied by concern (Jessen et al., 2020). In a certain proportion of individuals, SCD is considered the earliest preclinical indicator of AD, in that it is associated with increased likelihood of positive biomarkers and neurodegeneration consistent with AD pathology; for these cases, targeting preventive treatments at this stage holds the potential to slow or even prevent progression to dementia. Beyond its association with preclinical AD, there is another aspect of treating individuals with SCD, which is related to distressing symptoms that they experience. The self-perception of cognitive decline often leads to increased stress and fear of dementia, which in turn contribute to psychiatric symptoms like depression, anxiety, and apathy, generally and specifically related to subjectively perceived cognitive deterioration (Jessen et al., 2020). For instance, it has been demonstrated that concern about loss of cognitive function contributes to elevated anxiety observed in individuals with SCD, and anxiety in turn increases alertness for cognitive failures (Hill et al., 2016). As a result, SCD has also been associated with lower quality of life, reduced mental wellbeing perception and worsening of positive psychology constructs such as self-esteem and self-efficacy (Roehr et al., 2017; Su et al., 2023). All these factors, in turn, have a negative impact on brain structure and function, and increase the risk of cognitive decline and dementia. Therefore, early and effective preventive interventions could not only benefit the mental health of individuals with SCD but also potentially reduce the risk of future clinical progression.

Non-pharmacological interventions for SCD have received increasing attention in recent years. A meta-analysis by Sheng et al. (2020) of 18 randomized controlled trials investigating interventions for SCD (including psychological and health education, nutritional supplementation, cognitive training, and multi-domain interventions) found that cognitive training had a small effect on objective memory and significant improvements in subjective memory and psychological wellbeing. While some recent studies have corroborated the positive effects of cognitive training on cognitive function (Yu et al., 2024), others have reported conflicting results (Cheng et al., 2018; Hong et al., 2020; Bhome et al., 2018). Given the current lack of definitive evidence to guide recommendations and implement clinically practical interventions, further research is urgently needed.

Building upon recent advancements in computer technology, the emergence of new generations of Immersive Virtual Reality (IVR) has unlocked considerable potential for novel clinical applications (Tieri et al., 2018). These systems are particularly promising due to their capacity to offer greater ecological validity, allowing users to interact with virtual stimuli in a naturalistic manner using their own body movements, to experience the illusory sensation of “being physically present” in the virtual environment (i.e., sense of presence; Sanchez-Vives and Slater, 2005), and to enhance patient compliance (Tieri et al., 2018; Sanchez-Vives and Slater, 2005; Fusco and Tieri, 2022).

In light of the foregoing, this study aims to evaluate the effectiveness of an immersive virtual-reality (IVR) and telemedicine-based multi-component intervention, combining cognitive training and a health and lifestyle education program, on objective and subjective cognitive function, psychiatric symptoms, quality of life and brain connectivity in older adults at high-risk for cognitive decline and dementia (i.e., SCD). The primary objective is to determine whether the multi-component intervention, when compared to an active control condition, leads to significant post-intervention gains in objective cognitive functioning, and whether these gains are greater than those induced by a cognitive-only condition. The secondary objectives are: (1) to assess the transfer effect of the intervention on self-perceived cognitive functioning, psychiatric symptoms and quality of life; (2) to assess intervention-induced changes in whole-brain functional connectivity, as highlighted by resting state-fMRI images; (3) to assess user compliance with telemedicine approach combined with IVR. Exploratory objectives include: (1) investigating potential moderators of intervention efficacy (e.g., demographics, cognitive reserve, SCD severity, lifestyle and dementia risk factors); and (2) evaluating hypotheses regarding neuroimaging results and their association with behavioral data (e.g., correlation between behavioral and imaging data, association between post-training brain changes and participants' characteristics, and whether intervention-induced improvements rely on specialized brain areas or depend on compensatory responses from other regions).

## 2 Methods/design

### 2.1 Study design

This 5-week randomized controlled trial (RCT) use a double-blinded, three-parallel group design, guided in accordance with the Consolidated Standards of Reporting Trials (CONSORT) guidelines (Bennett, 2005). Following a screening phase to verify eligibility criteria through a comprehensive clinical and neuropsychological evaluation, and after obtaining informed consent, enrolled participants with SCD will undergo an in-person baseline assessment and a 3T MRI scan (where feasible) to collect clinical, neuropsychological, behavioral, and neuroimaging data prior to the intervention (T0). Then, using a stratified randomization method (ratio 1:1:1, taking age into account), participants will be allocated in a blinded fashion to one of the three experimental conditions:

(1) a multi-component intervention (MC-I), including SCD-tailored cognitive IVR training *plus* a health and lifestyle education program;(2) a cognitive-only intervention (CO-I), including SCD-tailored cognitive IVR training *plus* an active control for the education program;(3) an active control intervention (AC-I), including active controls for both cognitive training and education program.

The active control for the cognitive training (in the AC-I condition) involves IVR tasks mirroring the experimental training's structure but with very low cognitive demands. The active control for the education program (in both CO-I and AC-I conditions) consists of educational videos on topics unrelated to dementia and cognitive decline prevention. A detailed description of the interventions is provided in paragraph 2.7.

All three groups will receive 20 training sessions (4 sessions per week, each lasting about 30 min) over a period of 5 consecutive weeks. Participants will complete their respective interventions at home using virtual reality head-mounted displays (HMD) remotely controlled and monitored in real-time via a dedicated telemedicine platform. Prior to the intervention, all participants will receive in-person training on the use of HMD tool. Within 48 h and 1 week of completing the 5-week intervention, participants will return respectively for a post-intervention 3T MRI scan (where feasible) and an in-person evaluation, in order to collect post-training clinical, behavioral, neuropsychological and neuroimaging outcome measures (T1). A study flowchart is provided in Figure 1.

**Figure 1 F1:**
[figure not shown]
Flow diagram of the study design.

### 2.2 Participants

A sample of 75 individuals who refer to the Center for Cognitive Disorders and Dementias (CDCD) of IRCCS Santa Lucia Foundation because of a self-report of cognitive impairments and who meet the current criteria for SCD (Jessen et al., 2020) will be recruited. We are focusing on SCD subjects to be recruited from a memory clinic in accordance with evidence that help-seeking behavior in SCD has been related to a higher risk of progressive cognitive decline and dementia, as well as underlying AD pathology (Jessen et al., 2020). SCD will be defined in agreement with recently proposed recommendations (Jessen et al., 2020). Specifically, inclusion criteria are: (a) over 55 years of age; (b) absence of neurological or psychiatric disorders; (c) no history of alcohol or drug abuse; (d) Mini-Mental State Examination (MMSE) score ≥28; (e) age-appropriate cognitive functioning as confirmed by performance above the normality cut-off scores on all tests comprising the extensive neuropsychological battery administered during the screening phase (for details, see “*Neuropsychological screening battery”* section); (f) concern over a self-experienced cognitive decline. The latter will be operationalized with the following widely-used procedure (De Simone et al., 2023b). First, we ask participants “Do you feel like your cognitive ability (e.g., memory, concentration, planning, orientation, or language) has become worse?” (possible answers: yes/no). In case of a positive response we ask whether the perceived decline is experienced as worrisome by asking “Does this worry you?” (possible answers: yes/no). SCD will be defined by endorsement of perceived decline with concern about cognitive decline.

Additional inclusion criteria are ability to give their written consent to participate in the study, normal or corrected to normal vision and hearing, native or fluent proficiency in Italian, ability to commit to the whole intervention and follow-up assessment.

This RCT study is being conducted in accordance with the Declaration of Helsinki. The study protocol has been approved by the Territorial Ethics Committee of Lazio Area 5 (experiment register N.81/SL/23) and has been prospectively registered at ClinicalTrials.gov on May 24, 2024 (registration number: NCT06429215). Any significant changes in the protocol will be reported in the trial registry. Written informed consent will be obtained from each participant.

### 2.3 Sample size calculation

To estimate the appropriate sample size, the G^*^Power program was used. Considering an effect size of 0.37 obtained in a recent meta-analysis on cognitive intervention in SCD (Sheng et al., 2020), a power of 0.8 and an alpha of *p* < 0.05, we applied repeated measurements of multivariate analysis of variance (three groups: MC-I group, CO-I group, AC-I group; two measurements: pre-intervention and post-intervention) for analysis. The appropriate sample size was determined to be 74. Therefore, each of the three experimental groups requires at least 25 participants.

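### Section 2.3 takes 0.37 from a meta-analysis without naming its metric; 74 follows if it is used as Cohen's f, but if it is a standardised mean difference the stated 80% power is not delivered

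*Protocol article*

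**What the plan says.** Section 2.3 starts from one published figure: "Considering an effect size of 0.37 obtained in a recent meta-analysis on cognitive intervention in SCD". It sets "a power of 0.8 and an alpha of *p* < 0.05" and describes the procedure as follows: "we applied repeated measurements of multivariate analysis of variance", with three groups and "two measurements: pre-intervention and post-intervention". The result is "The appropriate sample size was determined to be 74", from which "each of the three experimental groups requires at least 25 participants". Allocation is equal across the arms (section 2.1).

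The section does not say whether 0.37 is a standardised mean difference, a Cohen's f or something else. It gives no conversion, no pre-post correlation and no assumed pattern of means across the three arms.

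Two other places bear on it. The Introduction cites the same meta-analysis and says that it "found that cognitive training had a small effect on objective memory". The last paragraph of the Introduction sets the primary objective as two questions about objective cognition: does the multi-component arm (MC-I) gain more than the active control (AC-I), and does it gain more than the cognitive-only arm (CO-I)?

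**The concern.** A pooled effect from two-arm trials is normally a difference between two means in SD units. The f that the power program asks for is the SD of the group means divided by the within-group SD, so the same number stands for a much larger separation between arms when it is read as f. If a mean difference went in as an f, the 80% belongs to a bigger effect than the one cited.

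The stated power governs how the result is read. If real power is well below 0.8, a non-significant result says little, and a reader who relies on section 2.3 could take it as evidence against benefit. The MC-I versus CO-I comparison is the most exposed: both arms receive the same cognitive training, and the calculation does not address that comparison at all.

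**Working it through.** **Inputs from the document.** Effect size 0.37, power 0.80, alpha 0.05, 3 groups, 2 measurements, N = 74, 25 per arm (all section 2.3); allocation 1:1:1 (section 2.1).

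**Inputs assumed.** Pre-post correlation ρ of 0.5 to 0.8, equal SDs at both visits, and, from step 3 on, 0.37 as a mean difference d in raw-score SDs.

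**1. Reproduce 74.** For the group-by-time interaction in a repeated-measures MANOVA with 3 groups and 2 times, df = (2, N − 3) and the noncentrality is λ = f²N. This equals a one-way ANOVA on change scores. With f = 0.37:

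- N = 73: power 0.797
- N = 74: power 0.803
- N = 75: power 0.809

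The first N to reach 0.80 is 74, as stated.

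A second route gives the same N. A repeated-measures ANOVA interaction with f = 0.37/2 = 0.185 and ρ = 0.5 has λ = 0.185² × N × 2/(1 − 0.5) = 0.1369N = 0.37²N, on the same df. Section 2.3 does not name that procedure or those inputs.

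**2. What f = 0.37 means with three arms.** In SDs of change, the gap between the extreme arms is:

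- one arm apart from two equal arms: 0.37 × 3/√2 = 0.78
- evenly spaced arms: 0.37 × √6 = 0.91

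Multiplying by √(2(1 − ρ)) gives raw-score SDs: about 0.61 to 0.70 at ρ = 0.7, and 0.50 to 0.57 at ρ = 0.8.

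**3. Power at N = 75 if d = 0.37.** Change-score SD = √(2(1 − ρ)). Then f = d/√6 (evenly spaced) or d√2/3 (one arm apart), divided by that SD. Pairwise power is for 25 versus 25, from the noncentral t.

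| ρ | f, even / one apart | Three-group power, even / one apart | MC-I vs AC-I power |
|---|---|---|---|
| 0.5 | 0.151 / 0.174 | 0.19 / 0.24 | 0.25 |
| 0.6 | 0.169 / 0.195 | 0.23 / 0.30 | 0.30 |
| 0.7 | 0.195 / 0.225 | 0.30 / 0.38 | 0.38 |
| 0.8 | 0.239 / 0.276 | 0.43 / 0.54 | 0.53 |

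Outside that range, three-group power is 0.54 / 0.68 at ρ = 0.85 and 0.73 / 0.85 at ρ = 0.9. With baseline adjustment instead of change scores it is 0.24 to 0.59 over ρ 0.5 to 0.8. A simulation of the one-apart pattern gave 0.248 at ρ = 0.5 and 0.539 at ρ = 0.8, in line with the table.

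Total N for 80% power on the three-group test would be 320 to 426 at ρ = 0.5, 194 to 257 at ρ = 0.7 and 130 to 172 at ρ = 0.8.

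**4. The pairwise questions, granting f = 0.37 in full.** With evenly spaced arms, MC-I versus CO-I is half of 0.91, or 0.45 SD of change. At 25 per arm its power is about 35%. It reaches about 78% only in the pattern where MC-I alone differs and CO-I equals control.

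**5. Detectable difference at 25 per arm, 80% power.** About 0.80 SD of the analysed quantity.

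- Change scores: 0.80 × √(2(1 − ρ)) = 0.80 raw SD at ρ = 0.5 and 0.51 at ρ = 0.8.
- Baseline adjustment: 0.80 × √(1 − ρ²) = 0.70 raw SD at ρ = 0.5 and 0.57 at ρ = 0.7.

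**The case against.** The stated N reproduces, so there is no slip in the computation itself. Nor does reproducing 74 prove that a mean difference was entered as an f: the route through f = 0.185 and ρ = 0.5 gives the same N, and it would be consistent with halving a mean difference first. That stands as a limit on the diagnosis. It does not rescue the power figure, because a 0.37 SD difference in gain at ρ = 0.5 still has only 19 to 24% power on the three-group test.

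A reader might infer that the protocol itself calls 0.37 small. It does not. The Introduction attaches that word to objective memory in the same meta-analysis, and section 2.3 does not say that 0.37 is that estimate. The tension is real but indirect. Part of it is also a matter of scale: 0.78 to 0.91 is in SDs of change, and the gap in raw SDs is smaller, though still above 0.37.

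The metric and ρ are assumptions, and at ρ = 0.9 power would be close to the claim. That is fair, so the consequences must stay conditional. The document offers no basis for so high a correlation.

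Sizing on the three-group test matches the analysis in section 2.9, and details of contrasts and multiplicity are commonly left to the analysis plan. Their absence here is not the point. The point is that the 80% in section 2.3 does not describe the comparisons named in the primary objective.

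**Conclusion.** The concern holds in conditional form. The procedure named in section 2.3 gives 74 when 0.37 is used as f, which implies a gap of 0.78 to 0.91 SD of change between extreme arms. If 0.37 is a standardised mean difference, power at N = 75 is about 0.19 to 0.54 for the three-group test and 0.25 to 0.53 for MC-I versus AC-I, over ρ 0.5 to 0.8. Independently of the metric, the stated 80% does not carry over to MC-I versus CO-I: it is about 35% with evenly spaced arms even at f = 0.37.

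Two stronger readings are not supported. One is that the trial's power is known to be 20 to 55%; that needs the metric and ρ, and the document gives neither. The other is that MC-I versus CO-I has almost no power. Figures of about 0.10 to 0.18 arise if half of a 0.37 SD effect is incremental, but that split is illustrative and nothing in the document fixes it.

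**What to change.** Keep N = 75 and revise section 2.3:

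- State the metric of 0.37 and which outcome in the meta-analysis it refers to.
- Convert it to the f of the group-by-time interaction, with an explicit pre-post correlation and pattern of means.
- Replace the 80% claim with the resulting power, or with the detectable difference at 25 per arm, separately for MC-I versus AC-I and MC-I versus CO-I. On change scores that difference is about 0.80 raw SD at ρ = 0.5 to 0.51 at ρ = 0.8; with baseline adjustment it is about 0.70 at ρ = 0.5 to 0.57 at ρ = 0.7.
- State that a non-significant MC-I versus CO-I result will be reported as inconclusive, with its confidence interval.
- Label any power figure that rests on a half-effect split as illustrative.

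The cost is a rewording of section 2.3 and of any matching text in the registry or analysis plan. No participants are added. The downside is that the stated power becomes less favourable.

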### 2.4 Neuropsychological screening battery

The tests comprising the standardized neuropsychological battery that is administered in the screening phase to assess inclusion criteria are described below according to the cognitive domains they examine:

(a) Global cognitive functioning: mini mental state examination (MMSE) (Magni et al., 1996);(b) Verbal episodic long-term memory: 15-word list test (immediate, 15-min delayed recall and 30-min recognition trial) and short story test (immediate and 20-min delayed recall; Carlesimo et al., 1996, 2002);(c) Short-term memory and working memory: digit span test forward and backward (Monaco et al., 2013);(d) Attention and Executive functions: phonological word fluency (Carlesimo et al., 1996), semantic word fluency test (Costa et al., 2014), modified card sorting test (Nocentini et al., 2002), trail making test parts A and B (Giovagnoli et al., 1996);(e) Reasoning: Raven's colored progressive matrices (Carlesimo et al., 1996);(f) Constructional praxis: copy of simple drawings and copy of drawing with landmarks (Carlesimo et al., 1996);(g) Language: naming subtest of the ENPA (NeuroPsychological Examination for Aphasia; Capasso and Miceli, 2001).

For all tests but one (i.e., ENPA naming) we use Italian normative data for score adjustment (sex, age, and education) and to define normality cut-off scores, which were established as the lower limit of the 95% tolerance interval for a confidence level of 95%.

